## Abstract

**Background:**

Menstrual pain which is severe enough to impact on daily activities is very common amongst menstruating females. Research suggests that menstrual pain which impacts on daily functioning may be even more prevalent amongst those with intellectual disabilities. Despite this, little research attention has focused on pain management programmes for those with intellectual disabilities.

The aims of this pilot study were to develop and evaluate a theory-based cognitive behavioural therapy (CBT) programme for menstrual pain management in young women with intellectual disabilities.

**Methods/Design:**

The study utilised a mixed methods controlled clinical trial to evaluate elements from a CBT programme called *Feeling Better* (McGuire & McManus, 2010). The Feeling Better programme is a modular, manualised intervention designed for people with an intellectual disability and their carers. The programme was delivered to 36 young women aged 12 – 30 years who have a Mild - Moderate Intellectual Disability, split between two conditions. The treatment group received the *Feeling Better* intervention and the control group received treatment as usual. To evaluate the effectiveness of the programme, measures were taken of key pain variables including impact, knowledge, self-efficacy and coping. Process evaluation was conducted to examine which elements of the programme were most successful in promoting change.

**Discussion:**

Participants in the intervention group were expected to report the use of a greater number of coping strategies and have greater knowledge of pain management strategies following participation in the intervention and at three month follow-up, when compared to control group participants. A significant advantage of the study was the use of mixed methods and inclusion of process evaluation to determine which elements of a cognitive behavioural therapy programme work best for individuals with intellectual disabilities.

**Trial registration:**

Current Controlled Trials ISRCTN75567759

## Background

The International Association for the Study of Pain (IASP) defines pain as “an unpleasant sensory and emotional experience associated with actual or potential tissue damage, or described in terms of such damage” [1]. Although definitions of what constitutes “chronic” pain vary, the IASP definition of pain lasting more than 3 months is widely accepted. Walsh, Morrison and McGuire [2] examined chronic pain in adults with an intellectual disability and found that chronic pain was experienced by 15% of adults with an intellectual disability, based on caregiver report. Whilst this is consistent with reports of the frequency of chronic pain in the general population, it has been suggested that this may be an under-estimate of the extent of the issue in those with intellectual disabilities, especially amongst those who are non-verbal or have a more severe level of disability [3]. As those with more severe intellectual disabilities are not always able to verbally communicate their pain to carers, their pain experience may not always be recognised and reported. Whilst the use of proxy respondents can also be beneficial in gathering information about the pain experience of those with significant intellectual disabilities and communication challenges, this method presents its own challenges including the issue of reliability of carer report. Other methods such as structured behavioural observation offer a reliable and valid alternative [4] and the use of more than one source of information increases the reliability of the information obtained.

Dysmenorrhea (menstrual pain) is extremely common with as many as 90% of menstruating female adolescents and 50% of women reporting that they suffer from it [5,6]. Kyrkou [7] examined how menstrual pain presents in women with intellectual disabilities as there is anecdotal evidence of an increase in this condition in this population but little research has been conducted in this area. The parents of 24 women with Down Syndrome or Autism Spectrum Disorder (ASD) were surveyed to ascertain how menstrual pain presents in women with intellectual disabilities. Results suggested that two thirds of the women with Autism, three quarters of the women with Down Syndrome and all of the women with Aspergers Syndrome appeared to have problematic period pain. These rates were higher than the 50% rate reported for women in the general population [6] however, due to the small sample size used in the study, caution is required in the interpretation of these findings.

Dysmenorrhea, defined as pain during menstruation which is severe enough to impact or interfere with daily activities [8] has recently been the focus of brain-imaging studies which have shown that the brains of otherwise healthy women with moderate-to-severe dysmenorrhea show significant differences in brain structure and function, when compared with non-dysmenorrheic women. Tu, Niddam and colleagues [9-11] identified differences in cerebral metabolism and cerebral structure for the trait of dysmenorrhea and between pain and pain-free states. Differences have also been found in neural activity induced by noxious skin stimulation when applied to areas remote from the pelvic/abdominal region, such as the arm [12]. An important aspect of these brain-imaging studies is that some of the differences in neural characteristics occurred chronically, throughout the menstrual cycle, even when dysmenorrheic women are not experiencing menstrual pain [13]. Berkley [14] suggests that the consistency of these findings along with those from individuals with other chronic pain conditions provides a strong argument that dysmenorrhea should be considered a chronic pain condition.

Given the potential for significant personal, social and economic impact from chronic pain, much research attention has been directed towards pain management and treatment options. In a review of psychological therapies for the management of chronic pain in the general population, Eccleston, Williams and Morley [15] found that CBT results in improvements in overall functioning and psychological wellbeing. There is also evidence of the effectiveness of such approaches for the treatment of dysmenorrhea [16].

There has been increasing interest in adapting CBT for use with people with an intellectual disability and a few authors have described the use of modified CBT. McCabe [17] described the effectiveness of treatment programmes for depression among adults with mild-moderate intellectual disabilities while Lindsay, Neilson and Laurensen [18] were successful in using this approach to treat anxiety in this population. Willner, Jones, Tam and Green [19] examined the efficacy of a cognitive-behavioural anger management group for individuals with an intellectual disability using a randomized controlled trial research design. They found that clients in the treated group improved on both self- and carer-ratings, relative to their own pre-treatment scores, and relative to the control group post-treatment. Individuals in the intervention group also showed further improvement relative to their own pre-treatment scores, at 3 month follow-up. McGuire and Kennedy [4] noted that there has been limited research evaluating CBT for chronic pain in people with an intellectual disability. An important advance in the area was the development of “*Feeling Better* – a manual for carers working with people who have intellectual disabilities and chronic pain” [20]. This modularised programme uses cognitive behavioural principles to teach individuals with intellectual disabilities a range of strategies to manage chronic pain more effectively. In a case series study by McManus and McGuire [21], some preliminary evidence was provided for the effectiveness of the programme with increases in participant scores on pain management knowledge, wellness-focused coping and effectiveness of coping following the intervention.

In view of the ample evidence that CBT can be used for chronic pain management including the management of dysmenorrhea in the general population, and the preliminary evidence for effectiveness in people with intellectual disability [21], there is a rationale for evaluating a CBT-based pain management programme for menstrual pain in women with an intellectual disability. This study will be the first controlled clinical trial to address the issue of menstrual pain management with individuals with intellectual disabilities. Research on pain in individuals with intellectual disabilities has largely focused on identification of pain and medical management of pain symptoms. Pain management has largely been ignored and pain management programmes have not routinely been offered to such individuals.

### Study aims & objectives

This pilot study aimed to evaluate if a theory-based cognitive-behavioural therapy programme for menstrual pain management (derived from the *Feeling Better* manual) is more effective than usual care in helping young women with intellectual disabilities to manage their menstrual pain. In order to answer this question, a small non-randomised controlled trial was conducted comparing the use of menstrual pain management programme with usual care in an intellectual disability service in the west of Ireland. The study included a number of potential secondary outcome measures in addition to the primary outcome measures of pain coping strategies used and pain knowledge. It will enable us to determine if:

1. Participation in the menstrual pain management group results in an increase in participants’ ratings of pain coping strategies, pain management knowledge and pain self-efficacy and if this is maintained at 3 month follow-up.

2. Participation in the menstrual pain management group results in a reduction in self-ratings of pain intensity and pain interference by participants and reduced ratings of pain intensity and pain interference amongst participants, as rated by their parents, and if these reductions are maintained at 3 month follow-up.

3. Participants whose parents score highly on pain-catastrophizing experience greater pain intensity and greater pain interference with quality of life. Catastrophizing – experiencing extremely negative thoughts about one’s plight and interpreting even minor problems as major catastrophes – appears to be a powerful way of thinking that greatly influences pain and disability and is important in determining one’s reaction to pain [22]. Goubert, Eccleston, Vervoort, Jordan and Crombez [23] found that parents’ catastrophic thinking about their child’s pain had a significant contribution in explaining the child’s disability and school attendance. For this reason, parental catastrophizing is expected to affect participants’ ratings of pain intensity, pain interference and pain coping strategies used.

4. Participants in the menstrual pain management group adopt more behavioural than cognitive coping strategies to manage their menstrual pain. Burkitt et al. [24] found that greater developmental level (rather than chronological age) was associated with the use of more cognitively demanding strategies as may be used in cognitive behavioural therapy treatment approaches. McManus and McGuire [21] also reported a marked absence of the use of cognitive coping skills. Participants were more likely to use behavioural strategies such as exercise and relaxation.

Process evaluation was conducted via qualitative focus groups with participants, parents and support staff. The purpose of this was to assess the acceptability of the intervention to participants, to explore their experiences including any suggestions they may have to further enhance the programme and to examine which elements of the programme were most successful in promoting change for young women with intellectual disabilities who experience menstrual pain. It was envisaged that this innovative approach would yield valuable information which could form the basis for effective interventions to enrich the quality of life of individuals with intellectual disabilities who experience menstrual pain, as well as enhancing the lives of their carers.

## Methods/Design

### Research design

This was a mixed methods study involving both quantitative and qualitative analysis. The sample size of N = 36 was achieved by delivering the pain management programme to three groups of participants in the intervention condition (18 participants in total). A comparison group contained another 18 participants with similar characteristics in terms of age, gender and level of cognitive ability. These individuals received treatment as usual during the study. This typically involved rest and medication, as required. On completion of the study, they will be offered the intervention.

The study design and methodology, based on the Medical Research Council’s (MRC) Framework for Evaluating Complex Interventions [25], was considered an exploratory clinical trial.

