### Treatment allocation and matching process

#### Intervention condition

Due to the logistics and practicalities of delivering an intervention group to individuals within a wide geographical sampling area, a non-randomised process was used to assign participants to the intervention group.

A list was compiled of all females attending a special class for students with a mild or moderate intellectual disability or a school for students with mild or moderate intellectual disabilities, who receive support services from the Brothers of Charity Services within County Galway. The Principals of five schools were contacted, informed of the research study and invited to participate in the study. Two schools agreed to participate and were assigned to the intervention group. Parents/Guardians of the relevant students were then contacted and asked for their consent for their daughters to participate. Once consent was granted, assent was obtained directly from the young women.

This treatment allocation methodology allowed for the delivery of the intervention during the school day, at the location where the young women received their day service. This minimised inconvenience and school absence for research participants. This approach also enabled the intervention to be delivered to participants at an appropriate space within the school timetable e.g. during Social, Personal and Health Education (SPHE) class and so ensured consistent attendance.

The same approach was used to recruit participants attending Adult Day Centres providing educational and training opportunities to young women with mild and moderate intellectual disabilities, who receive support services from the Brothers of Charity Services within County Galway.

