#### Intervention programme

The menstrual pain management intervention programme consisted of twelve sessions:

• Session 1: Psycho-education

• Session 2 – 4: Deep breathing, progressive muscular relaxation and guided visualisation

• Session 5: Taking exercise

• Session 6: Distraction techniques

• Session 7 – 9: How your thoughts make you feel, challenging negative thoughts and using positive coping strategies

• Session 10: Problem solving

• Session 11: Medication

• Session 12: Planning for the future

Each weekly session was conducted with a group of 5–7 young women and lasted approximately 45 minutes. The session structure consisted of a recap of the previous session and feedback on how participants used the new technique, general information, topic related examples, group exercises and discussion, homework exercises and a session summary sheet. At the end of each session, participants interacted during a snack break which fostered a sense of group cohesion.

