### Data analyses

#### Sample size and power calculation

There are a lack of well-conducted controlled trials and a lack of information about effect sizes of CBT with people with an intellectual disability within published research in this area. The authors were reliant on the few previous studies available regarding this area of research and for this reason, the feasibility study by Hassiotis et al. [35] was used as a guideline in calculating sample size requirement. This study proposed a total sample of 30 to be allocated across two conditions although there is currently discussion that feasibility trials ought to include up to 60 individuals. We based our sample size on the Hassiotis paper and allowed for 20% attrition, thus we recruited 36 participants across the treatment and control conditions, with n = 18 in each arm.

An *a priori* power analysis was conducted using G*Power [36]. With α = .05 (two-tailed), the proposed sample (*N* = 36) would detect moderate effects between groups (d = .50) with over 95% power using a repeated measures F test. A total sample of 16 participants would be needed to detect large effects (d = .8) with over 95% power using a repeated measures F test. For the regression analyses, a sample of 36 participants (α = .05) with three predictors would detect large effects (f^2^ = .35) with a power calculation of 80.95%, while six predictors would detect large effects with a power of 65.58%. The current sample was deemed appropriate as regression models with power less than 50% are deemed unreliable [37].

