#### Quantitative analysis

Multivariate analysis of variance (MANOVA) will be used to examine differences in the primary and secondary outcome measures between the intervention and matched control groups. Within-groups differences will be measured at each time-point, including baseline. Baseline scores will be included as a covariate to allow for regression to the mean and a multiple regression model will be used. A step-wise method of regression analysis will be conducted with predictors entered using the backward method. This method will be used for exploratory model building and will be cross-validated by then randomly splitting the data. The dependent variables of interest will be strategies used to cope with pain and pain knowledge. The reliability of the Pain Coping Strategies Questionnaire and the Pain Coping Scenarios Questionnaire will be assessed by Cronbach’s alpha and validity will be assessed by correlating the measures against one other. Predictors will include the demographic characteristics of age and degree of intellectual disability as well as time since onset of menstruation; frequency and duration of menstruation; number and frequency of menstrual symptoms experienced and history, treatment and use of medication to manage gynaecological problems and other medical conditions.

Process evaluation will be conducted to assess change over time for the primary outcome measures. This will be done by looking at within groups differences at each of the assessment time points. To assist with process evaluation, sessions 2 – 5 focused on behavioural coping strategies and sessions 7 – 10 were dedicated to cognitive coping strategies.

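### The intervention arm is three intact therapy groups, but the between-arm tests and the power figures assume 36 independent women; with positive within-group correlation the tests are anti-conservative

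*Protocol article*

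**What the plan says.** Under Research design, the sample was reached by "delivering the pain management programme to three groups of participants in the intervention condition (18 participants in total"), against 18 matched comparison participants on usual care. Under Intervention programme, "Each weekly session was conducted with a group of 5–7 young women". There were twelve weekly sessions, with group exercises, discussion and a break that encouraged group cohesion.

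Allocation was non-randomised and by site. Under Intervention condition, "Two schools agreed to participate and were assigned to the intervention group", and adult day centres were recruited in the same way. The Control condition section describes matched individuals and mentions no control groups.

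Under Quantitative analysis, "Multivariate analysis of variance (MANOVA) will be used to examine differences" between the arms, with baseline scores as a covariate and a multiple regression model. No term for therapy group or site is named.

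Under Sample size and power calculation, N = 36 "would detect moderate effects between groups (d = .50) with over 95% power using a repeated measures F test". For regression, 36 participants "with three predictors would detect large effects (f^2^ = .35) with a power calculation of 80.95"%, and six predictors give 65.58%. No ICC, design effect or clustering allowance appears.

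**The concern.** Women taught together for twelve weeks share the facilitator's delivery, the discussion and the setting. Two of the three primary measures record coping strategies and the third records knowledge of taught content, which are the things a group would learn in common. The groups also come from different schools and centres. A positive within-group correlation is therefore likely in the intervention arm.

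MANOVA and ordinary regression take their error term from variation between individuals. With positive correlation, the mean of 18 women in three groups is less precise than the mean of 18 unrelated women. The standard error of the arm difference is then too small, its confidence interval too narrow and its p-value too low. The study aims ask whether the programme beats usual care, and that answer depends on the standard error.

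**Working it through.** **1. The plan's own figures.** Inputs from the power section: α = .05, N = 36, f² = .35. For regression with p predictors, power is the upper tail of a noncentral F with λ = f²N = .35 × 36 = 12.6 and p and N − p − 1 degrees of freedom.
- p = 3 (df 3, 32): 80.95%, as stated.
- p = 6 (df 6, 29): 65.58%, as stated.

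Both match to the second decimal with 36 independent units and no design effect. The power figure over 95% does not come with the effect tested, the number of measurements or their correlation. One reading that satisfies it is a group-by-time interaction with f = d/2 = .25, five time points (which Table 1 gives for two of the three primary questionnaires) and an assumed correlation of 0.5. That gives 97.6%, again with 36 independent units.

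**2. Variance with clustering in the intervention arm only.** Three groups and 18 women give m = 18/3 = 6. The ICC is assumed.
- Design effect in the intervention arm: DE = 1 + (6 − 1) × ICC.
- With equal arms, the variance of the difference is inflated by (DE + 1)/2, and the standard error by the square root of that.
- Effective total N = 36 ÷ [(DE + 1)/2].

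Example at ICC .10: DE = 1 + 5 × .10 = 1.50; (1.50 + 1)/2 = 1.25; √1.25 = 1.12; 36/1.25 = 28.8.

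**3. Type I error.** This was simulated with 200,000 null trials: groups of 5, 6 and 7 against 18 independent controls, two-sample t-test at nominal 5%.

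| Assumed ICC | DE | SE factor | Effective N | Type I error |
|---|---|---|---|---|
| .01 | 1.05 | 1.01 | 35 | 5.3% |
| .05 | 1.25 | 1.06 | 32 | 6.5% |
| .10 | 1.50 | 1.12 | 29 | 8.1% |
| .20 | 2.00 | 1.22 | 24 | 11.3% |

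At ICC 0 the same simulation gives 5.0%.

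**4. Effect on power.** Putting the effective N into the interaction reading of step 1, 97.6% becomes about 97%, 96%, 93% and 87%. This is approximate, and is before the further loss from having only three clusters.

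**5. Can a mixed model estimate the clustering?** With three groups of six, the between-group variance estimate is zero or negative when the F ratio on 2 and 15 df is below 1. That ratio is an F(2, 15) variable multiplied by DE/(1 − ICC), so the chance is P[F(2, 15) < (1 − ICC)/DE]. In closed form this is 1 − (1 + 2x/15)^(−7.5) with x = (1 − ICC)/DE.
- ICC .05: x = .95/1.25 = .76, chance 52%.
- ICC .10: x = .90/1.50 = .60, chance 44%.
- ICC .20: x = .80/2.00 = .40, chance 32%.

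So in a third to a half of such trials the model would tend to collapse to the independence analysis. Otherwise few degrees of freedom remain: at ICC .10, a test on group means with Satterthwaite df has about 22% power for d = .5 in a simple post-test comparison.

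**The case against.** The article condenses a fuller plan, and silence about random effects is not proof that they are absent. That is a fair caution, but it does not dispose of the point: the article names its models and prints power figures that reproduce exactly under independence.

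The planned analysis adjusts for baseline, whereas the simulation is an unadjusted t-test on one outcome. Adjustment can absorb stable differences between sites, so the relevant ICC may be smaller than a raw one. This stands as a limit on the size. It does not reach correlation created by the sessions after baseline.

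The trial is an exploratory, non-randomised pilot, so little rests on an exact 5% level. That also stands, and it lowers the stakes. The article nevertheless asks an effectiveness question and claims high power.

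Three stronger readings are tempting and are not supported:
- A reader might infer that type I error certainly exceeds 5%. That needs a positive ICC, which the article does not give; at .01 the excess is negligible.
- A reader might cluster the controls too, which would give about 5.6%, 8.0%, 11.2% and 17.4% at the four ICCs. The Control condition section describes no control groups or sites, so these figures are hypothetical.
- A reader might extend the point to every analysis. The thematic analysis is unaffected.

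**Conclusion.** The point holds in conditional form. The stated between-arm tests and power figures assume 36 independent participants, while half the sample was treated in three intact groups from whole sites. If the within-group correlation is positive, the tests are anti-conservative. The excess runs from trivial (5.3% at ICC .01) to about double the nominal rate (11.3% at .20), with standard errors understated by factors of 1.01 to 1.22. These sizes rest on assumed ICCs, groups of about six, independent controls and no baseline adjustment. The direction is likely; the size is unknown and cannot be settled from three groups.

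**What to change.** 1. Keep the baseline-adjusted arm comparison. For each primary outcome, also report the confidence interval and p-value with the intervention-arm variance inflated at fixed ICCs of .01, .05, .10 and .20. With equal arms this multiplies the standard error by √[(DE + 1)/2]; use the actual group sizes.
2. A partially nested mixed model (random therapy-group effect in the intervention arm, small-sample degrees of freedom) may be added as supportive only, for the reason in step 5 of the working.
3. Restate in the power text that the quoted powers assume 36 independent participants, and that clustering lowers the effective sample size to about 32, 29 or 24 at ICC .05, .10 or .20.
4. Present the between-arm results as exploratory. Label the sensitivity analysis as added after data collection, because the Predictor variables section says pre- and post-intervention data are already in and analysis is under way.

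No new data are needed, provided group membership was recorded. The cost is wider intervals and less favourable power figures. None of this removes the confounding of site with arm, which should be stated as a separate limitation.
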